## 5.3 Randomization and Blinding

Potential trial participants were identified by a research team member through electronic medical record screening. Eligible patients were approached, and written informed consent was obtained either before surgery. Patients were randomly allocated in a 1:1 ratio to receive either the intervention group or the control group using Sun Yat–sen University Cancer Center' s (SYSUCC) interactive web–based response system (IWRS). Allocation concealment was ensured by restricting researcher access to the randomization system until study completion. An independent research assistant conducted randomization using sequentially numbered, opaque envelopes containing group assignments. Based on group assignments, the pharmacist prepared identical 5 mL intrathecal solutions (normal saline or morphine) in 10 mL syringes for administration. To ensure blinding, the administering anesthesiologist was excluded from subsequent procedures and data collection. An independent researcher, blinded to group allocation and uninvolved in interventions or analysis, collected all outcome data.

## 5.4 Study Variables

QoR–15[1]:QoR – 15 is a scale that comprehensively judges the quality of patients' postoperative recovery by evaluating five aspects of patients: pain, physical comfort, physical independence, psychological support, and emotional state. It has good validity, reliability, and clinical practicality.

127

128 NRS:NRS is a concise pain assessment scale that allows patients to quantify their pain  
129 intensity using a 0–10 numerical scale, commonly used for rapid measurement of  
130 pain severity in clinical settings.

131 MME:MME is a standard unit used to convert the doses of different opioid analgesics  
132 into equivalent morphine doses, facilitating clinical drug dosage adjustment and  
133 management.

134

135

136  
137

## 6 Sample Size

The primary outcome measure was the QoR-15 score at 24 h postoperatively. Based on previous literature and the results of pilot experiments, the minimum clinically important difference (MICD) of the QoR-15 score was determined to be 6.0. The standard deviation (SD) of the QoR-15 score after major surgery ranged from 10 to 16. Taking a conservative estimate, we selected an SD of 16. Assuming  $\alpha = 0.05$  and  $\beta = 0.2$  (with a power of 80% to detect this difference), calculations were performed using PASS 21 software. The result indicated that 113 patients were required in each group. Considering a 10% dropout rate, our target was a final sample size of 252.

## 7 General Considerations

Statistical analysis will be conducted in accordance with the plan outlined in the SAP. Statistical analysis will abide by these general statistical principles below.

### 7.1 Timing of Analyses

After all data have been collected and organized, statistics will be conducted.

### 7.2 Analysis Populations

Analysis will be performed 'Intention-to-treat'. All randomized subjects will be included in the final analysis.

### 7.3 Covariates and Subgroups

Covariates: Age, Gender, Weight, ASA, Complication, Duration of Anesthesia

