## 5.2 Inclusion–Exclusion Criteria and General Study Population

### Inclusion criteria:

Patients will be included if they had:(1) were scheduled for laparoscopic colorectal surgery, (2) provided consent for combined postoperative analgesia, (3) had an American Society of Anesthesiologists (ASA) physical status classification of I to III, and (4) were aged  $\geq 18$  years.

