### Exclusion criteria:

Patients will be excluded if they had:(1) declined surgery due to unforeseen circumstances or personal preference preoperatively, (2) had neurological dysfunction, (3) had contraindications to lumbar puncture, (4) had a history of preoperative opioid use, (5) reported baseline pain (assessed via the numerical rating scale [NRS]) with a score  $>3$ , or (6) required conversion to open surgery or secondary operation.

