## 188 8.2 Demographic and Baseline Variables

189 The following variables are considered to be demographic and baseline:

- 190 • Age, sex, height, weight, body mass index.
- 191 • History –Hypertension, Diabetes mellitus, Analgesic medications, Espiratory  
192 diseases
- 193 • ASA
- 194 • NRS
- 195 • Surgical type
- 196 • Duration of surgery, general anesthesia.

197

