## 198 9 Efficacy Analyses

199 This analysis adhered to the intention-to-treat (ITT) and per-protocol principle.  
200 Continuous quantitative data were described as mean  $\pm$  standard deviation if  
201 normally distributed, with between-group comparisons performed using  
202 independent t-tests. Non-normally distributed data were summarized as median  
203 (P25, P75) and analyzed using the Wilcoxon rank-sum test. Categorical variables  
204 were expressed as frequencies (percentages), with group comparisons conducted  
205 via Chi-square tests or Fisher's exact test, as appropriate. Ordinal data were  
206 similarly described as frequencies (%) and compared using the rank-sum test.

207 For the primary outcome, intergroup differences were assessed using a generalized  
208 estimating equation (GEE) model implemented via the R package geepack, with an  
209 exchangeable correlation structure. The model incorporated time, group, their  
210 interaction (time  $\times$  group), and adjustments for age, sex, weight, ASA classification,  
211 complications, anesthesia duration, and baseline values. Estimated marginal means  
212 at each time point were visualized using line plots, either as absolute values or  
213 relative changes from baseline.

214 Binary outcomes were reported as counts (%) and analyzed using generalized linear  
215 models to estimate rate differences (RDs) with 95% CI, adjusting for age, sex,  
216 weight, ASA status, complications, and anesthesia duration. For ordinal outcomes,  
217 between-group comparisons employed the rank-sum test, with median differences  
218 and 95% CI calculated. Single-measurement continuous outcomes were analyzed via

219 linear regression, adjusting for the same covariates.

220 Longitudinal outcomes lacking baseline measurements were evaluated using GEE  
221 models (exchangeable correlation) with time, group, their interaction, and  
222 covariates (age, sex, weight, ASA, complications, anesthesia duration). Estimated  
223 trends were plotted by group. All analyses and visualizations were performed in R  
224 (v4.4.1).

225 Results of efficacy analyses will be presented as tables or in text in the final  
226 publication(s), including p-values.

227 9.1 Primary Efficacy Analysis

228 Analysis of primary endpoint (xx) will be performed in accordance with section 9.

229 9.2 Secondary Efficacy Analyses

230 Analyses of secondary endpoints will be performed in accordance with section 9.

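### Surgical type is listed as a baseline variable but left out of the adjusted models, which may forgo a small gain in precision and leaves chance imbalance in operation mix only partly adjusted

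*SAP*

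**What the plan says.** Inclusion criterion 1 in SAP section 5.2 takes patients who "were scheduled for laparoscopic colorectal surgery", with no restriction by type of operation. The only exclusion that concerns the procedure itself is for patients who "required conversion to open surgery or secondary operation".

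On allocation, section 5.3 says: "Patients were randomly allocated in a 1:1 ratio to receive either the intervention group or the control group". It names no stratification factor.

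Section 8.2 includes "Surgical type" among the demographic and baseline variables. It does not define the levels or say whether the scheduled or the performed operation is meant.

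The adjustment set in section 7.3 reads "Covariates: Age, Gender, Weight, ASA, Complication, Duration of Anesthesia". In section 9 the primary GEE uses these six and ends its list with "complications, anesthesia duration, and baseline values". Longitudinal outcomes without a baseline measurement are adjusted for "covariates (age, sex, weight, ASA, complications, anesthesia duration"). The linear regressions for single-measurement outcomes and the rate-difference models use the same six. Surgical type is in none of these lists.

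**The concern.** Having decided to adjust, the plan leaves out the variable that describes which operation the patient is to have. The scheduled operation is fixed before allocation and cannot be affected by it. Anesthesia duration, which is in the list and may partly stand in for operation type, is known only after allocation.

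If recovery differs between, say, colon and rectal operations, two things follow. The variation that the other covariates do not pick up stays in the residual and widens the confidence interval slightly. A chance difference in operation mix between arms is also corrected only as far as the other covariates track operation type. The secondary outcomes have less protection than the primary one, because time to flatus, ambulation, length of stay and opioid use have no baseline measurement in their models.

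**Working it through.** **Inputs from the SAP.** Target difference 6.0 points and SD 16, the top of a stated range of 10 to 16; alpha 0.05, power 80%, 113 per group, 10% dropout, total 252 (section 6). Two-sided testing (section 7.6).

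**The plan's own figure.** Normal approximation: n = 2 × (1.96 + 0.842)² × 16² / 6² = 111.6, so 112 per group. The two-sample t-test gives 112.6, so 113. With dropout, 113 / 0.9 = 125.6, so 126 per group and 252 in total. The stated sample size reproduces. It uses an unadjusted SD, so it takes no credit for any covariate.

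**Assumption needed.** The SAP gives no QoR-15 difference by operation type. Let R² be the share of the remaining outcome variance that surgical type explains, with an assumed range of 0.01 to 0.10. For two equally common types that differ by d points, R² = 0.25 × d² / 16². This gives 0.9% at d = 3 and 9.8% at d = 10, so the range corresponds roughly to gaps of 3 to 10 points.

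**Precision and power at 113 per group.** Residual SD = 16 × √(1 − R²). Half-width of the 95% CI = 1.96 × residual SD × √(2/113). Power is from the t-test for a difference of 6.

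| Assumed R² | Residual SD | Half-width | Power |
|---|---|---|---|
| 0 | 16.00 | 4.17 | 80.1% |
| 0.01 | 15.92 | 4.15 | 80.5% |
| 0.02 | 15.84 | 4.13 | 80.9% |
| 0.05 | 15.59 | 4.07 | 82.1% |
| 0.10 | 15.18 | 3.96 | 84.1% |

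The standard error falls by 1 − √0.99 = 0.5% at R² = 0.01 and by 1 − √0.90 = 5.1% at R² = 0.10.

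**Chance imbalance.** Suppose a two-level type with prevalence q and simple randomization. The SD of the between-arm difference in prevalence is √(2q(1 − q)/113), which is 0.061 at q = 0.3 and 0.067 at q = 0.5. The 95% limits are about ±0.12 and ±0.13. Multiplied by an assumed gap of 3 to 8 points, the shift in an unadjusted difference lies within:

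- q = 0.3: ±0.36 (3 points) to ±0.96 (8 points)
- q = 0.5: ±0.39 (3 points) to ±1.04 (8 points)

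That is about ±0.4 to ±1.0 points against a target of 6.0. These figures are for an unadjusted comparison. In the adjusted primary model the shift would be smaller to the extent that baseline QoR-15, ASA and anesthesia duration track operation type.

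**The case against.** The strongest reply is that this is a preference about covariates and not an error. Sections 7.3 and 9 agree with each other. Listing a variable in section 8.2 does not commit the plan to adjusting for it: height, body mass index, hypertension, diabetes and NRS are also listed there and not named as covariates. This stands, and the point is not a contradiction in the document.

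A reader might also infer something stronger: that known case-mix variation is left wholly in the error term, that chance imbalance goes uncorrected, or that the result is biased or the trial underpowered. The SAP does not support these readings.

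- It nowhere says that QoR-15 or any other outcome differs by operation, or that patients vary most on this characteristic. The prognostic role is plausible, not documented.
- The primary model already contains baseline QoR-15, ASA and anesthesia duration, which may absorb part of any such effect.
- Under randomization, leaving a prognostic covariate out of this linear comparison neither biases the estimate nor inflates the type I error. The confidence interval already allows for chance imbalance.
- Planned power does not depend on this adjustment, as the reproduced sample size shows.

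Two further cautions hold. Stratification may be described in the protocol, which is not at hand. If allocation was stratified by operation, the factor would normally belong in the model anyway, so the same change would apply. Section 8.2 also does not show that the scheduled operation is what was recorded.

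The case for the change survives on a small scale. Anesthesia duration is only a post-allocation stand-in for operation type, and the secondary outcomes named above have no baseline term to absorb case mix.

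**Conclusion.** The point holds as a minor efficiency improvement. The plan's validity and its planned power are intact. If surgical type explains 1% to 10% of residual variance, adjusting for it would reduce the standard error by about 0.5% to 5% and lift power at 113 per group from 80.1% to between 80.5% and 84.1%. It would also address directly a chance imbalance in operation mix that could move an unadjusted difference by up to about 0.4 to 1.0 points. Both ranges rest on assumed differences between operation types, because the SAP gives none. If operation type is unrelated to outcome once the other covariates are in the model, there is essentially nothing to gain.

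**What to change.** Before unblinded analysis, add surgical type to the covariate list in section 7.3. Define it as the scheduled operation, so that assignment cannot affect it, and code it in a few prespecified levels, for example colon versus rectal. Carry it into the primary GEE and into the continuous and longitudinal secondary models in section 9. State in section 8.2 that the scheduled operation is meant, and confirm that it is recorded or can be recovered from preoperative records. Adding the term only after an imbalance has been seen would make it post hoc.

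The cost is a few words in the SAP and one degree of freedom for two levels, or a few for more. The rate-difference models for infrequent adverse events may leave the term out if they do not converge, and the SAP should say so in advance.

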### 7.4 Missing Data

The missing values in Full Analysis Set will not be imputed.

### 7.5 Interim Analyses

Interim analyses are not planned.

### 7.6 Confidence Intervals and p-values

All estimates of differences between groups would be presented with two-sided 95% confidence intervals unless otherwise stated. Statistical significance will be considered if  $p < 0.05$  (two-sided).

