### 4.2 Endpoints

#### Primary endpoint:

The primary endpoint is the QoR-15 score at 24 h postoperatively.

Definition : QoR – 15 is a scale used to assess the quality of postoperative recovery. It was developed by McDowell and his team in Sweden in 2005 and is a simplified version of the QoR scale. QoR – 15 consists of 15 items and 5 domains, namely physical state, cognitive state, emotional state, social state, and pain state. It assesses the quality of postoperative recovery by measuring the patient's self – perceived psychological and social function states. Each item is scored on a 10 – point scale, with a total score of 150 points. The higher the score, the better the recovery quality.

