#### Secondary endpoints:

- 1) QoR-15 scores at 48 and 72 h postoperatively,
- 2) cumulative opioid consumption (MME) at 24, 48, and 72 h postoperatively,
- 3) total intraoperative opioid dosage,
- 4) NRS scores during rest or movement in the post-anesthesia care unit (PACU) or at 24, 48, and 72 h postoperatively,
- 5) time to first flatus,
- 6) time to first ambulation,
- 7) supplementary analgesic dosage at 24, 48, and 72 h postoperatively,
- 8) adverse events (dizziness/headache, nausea/vomiting, pruritus, hypotension) at 24, 48, and 72 h postoperatively and
- 9) length of hospital stay.

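### One p < 0.05 rule covers all 32 secondary comparisons, with no testing order, adjustment or descriptive label

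*SAP*

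**What the plan says.** Section 4.2 names one primary endpoint at one time: "The primary endpoint is the QoR-15 score at 24 h postoperatively". Nine secondary items follow. Some are single measurements, such as "total intraoperative opioid dosage". Others are spread over time, such as "QoR-15 scores at 48 and 72 h postoperatively", "cumulative opioid consumption (MME) at 24, 48, and 72 h postoperatively" and "NRS scores during rest or movement in the post-anesthesia care unit (PACU) or at 24, 48, and 72 h postoperatively".

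Section 7.6 gives the inferential rules. On estimation: "All estimates of differences between groups would be presented with two-sided 95% confidence intervals unless otherwise stated". On testing: "Statistical significance will be considered if" p is below 0.05, two-sided. Neither sentence separates primary from secondary endpoints.

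Sections 9.1 to 9.3 send the primary, secondary and exploratory analyses to the common methods of section 9, and section 10 does the same for adverse events. Section 9 says that efficacy results will appear in tables or text of the final "publication(s), including p-values". The SAP contains no testing order, gate, division of alpha or multiplicity adjustment, and does not call the secondary results descriptive or exploratory.

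**The concern.** The trial is sized for one test at the 5% level. Applied as written, the rule in 7.6 also allows a secondary result to be called statistically significant whenever its unadjusted p-value falls below 0.05, whether or not the primary comparison succeeds. A difference in 72 h pain, time to flatus or pruritus could then be reported in the same terms as the primary result, and the SAP gives the reader no prespecified basis for weighing it differently.

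This is not simply detail left to a protocol. The SAP has a section on p-values, and the rule stated there has no limit. What is at stake is which conclusions the trial may draw from its secondary endpoints; no estimate and no part of the primary test is affected.

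**Working it through.** **The plan's own figure.** Section 6 gives a difference of 6.0, SD 16, alpha 0.05 and power 80%. The normal approximation with two-sided alpha is n = 2 × (1.960 + 0.842)² × 16² / 6² = 111.6, so 112 per group. The t-test version gives 112.6, so 113, as stated. With 10% dropout, 113 / 0.90 = 125.6, so 126 per group and 252 in total, as stated. The calculation uses the full 5% for the single primary test.

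**Count of secondary comparisons (section 4.2).**

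| Item | Comparisons |
|---|---|
| QoR-15 at 48, 72 h | 2 |
| Cumulative MME at 24, 48, 72 h | 3 |
| Intraoperative opioid | 1 |
| NRS, rest and movement, at PACU, 24, 48, 72 h | 2 × 4 = 8 |
| First flatus | 1 |
| First ambulation | 1 |
| Supplementary analgesic at 24, 48, 72 h | 3 |
| Adverse events, 4 types at 24, 48, 72 h | 4 × 3 = 12 |
| Hospital stay | 1 |
| **Total** | **32** |

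Four of the nine items (MME, NRS, supplementary analgesic, adverse events) have three or four time points. Without adverse events, 32 − 12 = 20 comparisons remain.

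**Expected false positives if no effect exists on any of them.** This is k × 0.05, whatever the correlation: 32 × 0.05 = 1.6 and 20 × 0.05 = 1.0.

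**Chance of at least one, independent tests.** This is 1 − 0.95^k:

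- k = 32: 1 − 0.95^32 = 0.81
- k = 20: 1 − 0.95^20 = 0.64
- k = 9 (one test per listed item): 1 − 0.95^9 = 0.37

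**Chance of at least one, correlated tests.** The SAP gives no correlations, so these values are assumptions. They come from simulating 32 two-sided z-tests with no true effect (400,000 draws per scenario).

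| Assumed correlation | Chance of at least one p < 0.05 |
|---|---|
| Exchangeable 0.1 | 0.79 |
| Exchangeable 0.3 | 0.68 |
| Exchangeable 0.5 | 0.52 |
| Exchangeable 0.7 | 0.35 |
| Exchangeable 0.9 | 0.17 |
| Within outcome 0.5, between outcomes 0.1 | 0.74 |
| Within 0.7, between 0.3 | 0.61 |
| Within 0.9, between 0.3 | 0.53 |
| Within 0.9, between 0.5 | 0.43 |

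Even the lowest entry, 0.17, is more than three times 0.05.

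**The case against.** The strongest reply is that the trial has one primary endpoint at one time, is sized on it alone, and labels everything else secondary. In such trials unadjusted secondary p-values are commonly reported as supportive. Printing a p-value is not a confirmatory claim, and 7.6 already promises confidence intervals. Much of this stands: the endpoints do have a ranking, and what is missing is only a rule for interpreting those below the primary. But the SAP does not say that the secondary results are supportive, and its one rule on significance makes no exception for them.

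A second reply is that 32 is a choice. Section 9 fits one GEE model to each longitudinal outcome and does not say that every time point carries its own claim. Adverse events also come under safety in section 10, where familywise control is not normally sought because missing a harm matters more. Both points are fair, which is why the figures for 20 and for 9 tests are given. Against them, section 4.2 writes the time points into the endpoints and lists adverse events among the secondaries. The count could also be higher: section 9 names both intention-to-treat and per-protocol analyses and describes simple tests beside adjusted models, and the schedule in section 5.1 shows two length-of-stay columns.

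A third reply is that independence is not credible. Cumulative MME at 48 h contains the 24 h amount, and pain is scored repeatedly in the same patients. This stands. The figure of 0.81 belongs at the upper end of a range.

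**Conclusion.** The point holds as a gap in how secondary results may be interpreted. As written, the SAP allows an unadjusted claim of significance on any of 32 secondary comparisons. With no effect on any of them, 1.6 false claims are expected (1.0 without adverse events). The chance of at least one is 0.81 under independence and about 0.35 to 0.79 for exchangeable correlations of 0.7 down to 0.1.

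Two stronger readings are tempting, and the document supports neither.

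- A reader might infer that the trial's main conclusion is compromised. It is not: the primary endpoint is one score at one time, and the secondary tests do not change its 5% error.
- A reader might infer that a false claim is likely in this trial. That requires most of the secondary null hypotheses to be true and the correlation to be modest. Under independence at least 14 true nulls are needed to pass 50% (1 − 0.95^13 = 0.49; 1 − 0.95^14 = 0.51). If the treatment truly affects many of these outcomes, there are fewer opportunities for a false positive.

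The change should be made, because it decides what may be concluded from the secondary endpoints and needs only wording.

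**What to change.** Replace the significance sentence in section 7.6 with:

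> The p < 0.05 rule applies only to the 24 h QoR-15 group contrast. Secondary and exploratory results are reported as estimates with 95% CIs, not adjusted for multiplicity, and are not used to claim statistical significance; adverse events are summarised descriptively with 95% CIs.

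Any p-values still printed for secondary endpoints under section 9 should carry the same statement that they are unadjusted.

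The cost is wording in the SAP, and the sponsor gives up the term 'significant' for secondary results. The sample size stays at 113 per group and 252 in total, because the primary test keeps its full 5%.

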## 8 Summary of Study Data

All continuous, normally distributed variables will be summarized using the following descriptive statistics: n (non-missing sample size), mean, standard deviation (SD). All continuous, not-normally distributed variables will be summarized using the following descriptive statistics: n (non-missing sample size), median, interquartile range (IQR). The frequency and percentages (based on the non-missing sample size) of observed levels will be reported for all categorical measures of baseline characteristics. Moreover, for dichotomous outcomes point estimates and 95% CI and absolute differences as difference of percentage points and 95% CI will be calculated. All summary tables will be structured with a column for each treatment in the order (Control, Intervention) and will be annotated with the total population size relevant to that table/treatment.

